## Abstract

**Background:**

Tracheal intubation with the patient in the lateral position is difficult because the laryngeal view is compromised during direct laryngoscopy. Flexible video endoscopes may facilitate intubation even when laryngeal views are poor on direct laryngoscopy because the patients are positioned laterally. Thus, this trial aims to compare the efficacy of flexible video endoscopes to Macintosh laryngoscopes for orotracheal intubation in the lateral position and to investigate their feasibility, i.e., whether the use of the two devices in combination can secure the airway when endotracheal intubation in the lateral position has failed using one device.

**Methods:**

This will be a prospective, randomized, single-center, clinical trial. One hundred and seventy-four patients aged 18–65 years, who have been scheduled to undergo tracheal intubation under uniform general anesthetic techniques for elective kidney surgery in the lateral decubitus position will be randomly divided into the flexible video endoscope and the Macintosh laryngoscope groups. Primary outcomes include intubation time and intubation success rate. Secondary outcomes include overall user satisfaction (graded from 1 to 10 (1 = very poor, 10 = excellent)) and perioperative side effects and complications, such as frequency of esophageal intubation, lip or dental injury, sore throat, and hoarseness.

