### Study outcomes

The primary outcome is the intubation success rate. Secondary outcomes include the intubation time, the anesthesiologist’s evaluation of the ease of the technique (using a visual analog scale (VAS) 0–10 [11]), and perioperative side effects and complications. Frequency of esophageal intubation, lip or dental injury, sore throat, and hoarseness will be recorded by a non-blinded observer. Intubation time will be measured using a stopwatch, and each failed intubation attempt will be recorded as 61 s. Secondary outcomes also include the intubation success rate of the combined use of the Macintosh laryngoscope and flexible video endoscope during the second attempt. The patients will be followed up for 24 h after surgery. 

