### Statistical analysis

The minimum sample size is estimated on the basis of intubation success rate. Based on previous reports of a 85.3% intubation success rate using the Macintosh laryngoscope with the patient in the lateral position [2] and a 97% intubation success rate using the flexible video endoscope with the patient in the lateral position [7], assuming that 10% of participants would drop out, 87 patients would be required in each group to detect such a difference with a significance level of 5% and power of 80%. PASS 11 (NCSS, LLC; Kaysville, UT, USA) was used for the sample size calculation. Demographic data will be compared using Student’s *t* test. Time to intubation and overall user satisfaction score will be analyzed using the Mann–Whitney U test. Comparison of various rates will be performed using the chi square (χ^2^) test with Yates correction or Fisher’s exact probability test. A *P* value <0.05 is considered statistically significant.

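### The abstract ranks intubation time as a primary outcome, while the outcomes section ranks it as secondary and makes success rate the only primary outcome

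*Protocol article*

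**What the plan says.** Three places in the protocol article bear on the rank of intubation time.

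- Abstract, Methods: "Primary outcomes include intubation time and intubation success rate". The next sentence there lists the secondary outcomes (user satisfaction, side effects and complications), and time is not among them.
- Study outcomes: "The primary outcome is the intubation success rate. Secondary outcomes include the intubation time". One outcome is primary here, and time is moved down a rank.
- Statistical analysis: "The minimum sample size is estimated on the basis of intubation success rate". The planning values are two success rates, 85.3% and 97%. No assumption about time enters the calculation.

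The Statistical analysis section assigns the Mann–Whitney U test to time and a Yates-corrected chi-square or Fisher's exact test to rates, with one threshold of P<0.05. The limitations paragraph of the Discussion makes clear that success means success at the first attempt only.

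**The concern.** The primary outcome determines what the trial may conclude. Suppose the success rates do not differ significantly but the intubation times do. Under the abstract, that could be reported as a positive result on a primary outcome. Under the Study outcomes section it would be a secondary finding in a trial that missed its primary outcome. An article that supports both readings leaves room to choose between them once the data are known. The Trial status section says that recruitment is under way, so the rank should be settled now.

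This is more than abbreviation in an abstract. The abstract gives separate lists of primary and secondary outcomes and puts time in the first. Nor is it detail left to a fuller document, because the article makes two opposite statements about the same item.

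**Working it through.** **1. The statements side by side**

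| Place | Success rate | Intubation time |
|---|---|---|
| Abstract, Methods | primary | primary |
| Study outcomes | primary (only one) | secondary |
| Statistical analysis, sample size | basis of N | not used |

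The two body sections agree with each other. The abstract is the outlier, and only on time.

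**2. The plan's own figure**

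Inputs (Statistical analysis): p1 = 0.853, p2 = 0.97, difference 0.117, mean 0.9115, α = 0.05 (taken as two-sided), power 0.80, 10% dropout.

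Pooled normal formula: n = [1.960·√(2·0.9115·0.0885) + 0.842·√(0.853·0.147 + 0.97·0.03)]² / 0.117² = (0.787 + 0.331)² / 0.01369 ≈ 91.3, so 92 per group. With dropout, 92/0.9 = 102.2, so 103.

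The stated 87 per group is not reproduced once dropout is included. The other variants tried (unpooled, arcsine, exact power, one-sided, continuity-corrected) did not give it either. That is a separate matter. What counts here is that success rate is the only outcome in the calculation.

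**3. Error rate under each reading (no true difference)**

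- Success rate as sole primary outcome (body text): one test at 5%, so the level holds.
- Both primary, both required: at most 5%.
- Both primary, either sufficient: at most 0.05 + 0.05 = 10%; if the tests were independent, 1 − 0.95² = 9.75%.

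The third case was simulated with 78 evaluable patients per group (87 × 0.9 = 78.3). Failures were entered as 61 s, as the article prescribes. Times for successes were *assumed* log-normal with median 30 s and log-scale SD 0.3, since the article gives no distribution. There were 10,000 runs per row.

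| Common success rate | Yates test alone | Mann–Whitney alone | Either (Yates) | Either (uncorrected chi-square) |
|---|---|---|---|---|
| 0.853 | 2.6% | 4.9% | 6.6% | 8.5% |
| 0.91 | 2.6% | 4.8% | 6.9% | 9.0% |
| 0.97 | 0.7% | 5.3% | 6.0% | 9.4% |

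The last column is for contrast only, because the plan does not name an uncorrected test. A further check with Yates and Fisher, 78 and 87 per group, and log-scale SDs of 0.2 to 0.5 stayed within about 5–8%. The result is below 9.75% mainly because the Yates and Fisher tests are conservative at these success rates, and partly because the two outcomes share the failures.

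**4. Could the readings lead to different conclusions in practice?**

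Exact power of the Yates-corrected test for 85.3% against 97% is 71% at 87 per group and 67% at 78. So even if the planning assumption is true, the success-rate test misses significance in 29–33% of trials. Those are the trials in which the rank of time would matter.

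**5. If two primary outcomes had been intended**

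Splitting α to 0.025 each changes 1.960 to 2.241: n = (0.900 + 0.331)² / 0.01369 ≈ 110.7, so 111 per group, or 111/0.9 = 123.3, so 124 with dropout. The planned 87 does not provide for this.

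**The case against.** The strongest reply is that the operative text does fix the primary outcome. The section devoted to outcomes names one, the sample size is built on it, and the Discussion defines it as first-attempt success and frames the expected benefit as greater success. A single abstract sentence stands against all of this. This largely stands, and it makes the right correction plain. It does not remove the contradiction.

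A reader might go further and infer that the 5% error rate is not held. The documents do not support that. Inflation needs two things together: that the abstract overrides the body, and that significance on either outcome is enough. The article does not state the second.

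A reader might also object that there is no rule for discordant results or for multiplicity. With one primary outcome none is needed, and for co-primary outcomes such a rule would commonly sit in an analysis plan that is not shown. Coding failures as 61 s is openly stated and does not affect the error rate of a success-rate primary test. Finally, a switch of outcome is a possibility that the wording leaves open. Nothing in the article shows that one has occurred.

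**Conclusion.** The article is wrong as written: the abstract and the Study outcomes section give intubation time incompatible ranks. Because this decides what counts as a positive trial, it should be corrected before analysis. The finding rests on the text alone and needs no assumption.

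The effect on the error rate is conditional. It is nil on the body's reading. It is roughly 5–8% in place of 5% if the abstract governed, either outcome sufficed, and the planned Yates or Fisher test were used with log-normal times, with an upper bound near 10% whatever the distribution. No part of the design in the body needs to change.

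**What to change.** Correct the Methods paragraph of the abstract so that first-attempt intubation success rate is the single primary outcome and intubation time is listed with the secondary outcomes, in line with the Study outcomes and Statistical analysis sections. Add one sentence to the Statistical analysis section saying that the trial's confirmatory conclusion rests on the success-rate test alone. Check that the registry entry, which is not among the documents at hand, gives the same rank.

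The cost is two sentences. Sample size, tests and conduct are unchanged. What is given up is the option of claiming a time difference alone as a primary result.

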**Discussion:**

The trial will clarify the efficacy of intubation with a Macintosh laryngoscope and a flexible video endoscope in the lateral position, and whether the two devices could be used in combination to secure the airway in cases where endotracheal intubation in the lateral position has failed with one device.

**Trial registration:**

Chinese Clinical Trial Register, ChiCTR- IOR-15007175. Registered on 6 October 2015.

**Electronic supplementary material:**

The online version of this article (10.1186/s13063-019-3263-1) contains supplementary material, which is available to authorized users.

## Background

In certain situations, patients require emergency endotracheal intubation to maintain airway patency in the lateral position, such as in accidental pulling out of the endotracheal tube during surgery, inadequate regional anesthesia that warrants general anesthesia, and intubation in the presence of bleeding in the airways above the larynx to prevent the risk of aspiration [1, 2]. Sometimes, clinicians may encounter a clinical situation where the supine position is not possible, such as a patient’s inability to lie down in the supine position because of a large lumbar mass, and the airway then has to be secured with the patient in the lateral position [3]. Moreover, patients undergoing surgical procedures in the lateral position may benefit from endotracheal intubation performed in the lateral position because it avoids the risk of adverse events caused by switching an anesthetized patient from the supine to any other position [4, 5]. Direct laryngoscopic intubation, as typical airway management, is more challenging in the lateral position than in the supine position primarily because of the distorted airway anatomy and unfamiliar posture that is necessarily required of the operating medical personnel [6].

When patients undergo gastroscopy under propofol anesthesia in the lateral position, the glottis is easily exposed just before the gastrointestinal endoscope passes through the esophageal inlet. A recent report compared the use of a fiberoptic bronchoscope in the supine and lateral positions, and revealed that endotracheal intubation using a fiberoptic bronchoscope might be an effective and timesaving technique for patients in the lateral position [7]. However, use of the flexible video endoscope and Macintosh laryngoscope have not been compared in the lateral position in prospective trials. The flexible video endoscope used in this clinical trial is very similar in structure and function to a fiberoptic bronchoscope. Our hypothesis is that the differences in construction and operational features of the Macintosh laryngoscope and the flexible video endoscope would result in differences in clinical performance in patients in the lateral position.

In a population of patients with low a priori predicted risk of difficult airway control, we sought to (1) compare the effects of intubation with a Macintosh laryngoscope to the effects of intubation with a flexible video endoscope with the patient in the lateral position and (2) investigate the feasibility of endotracheal intubation by combining the use of the Macintosh laryngoscope and a flexible video endoscope, i.e., determine whether the use of both devices in combination could secure the airway when endotracheal intubation in the lateral position has failed using one device.

## Methods

The study will be conducted at the First Affiliated Hospital of Fujian Medical University (Chinese Clinical Trial Register, ChiCTR- IOR-15007175). The study protocol was prospectively approved by the First Affiliated Hospital of Fujian Medical University Ethics Committee.

One hundred and seventy-four patients with American Society of Anesthesiology (ASA) physical status I–II, aged 18–65 years old, who are scheduled for elective kidney surgery in the lateral decubitus position and require endotracheal intubation for general anesthesia will be enrolled in this study. Patients with a body mass index (BMI) > 30 kg/m^2^, cervical spine abnormality, pharyngolaryngeal disorder, anticipated difficult-to-intubate airway, or increased risk of aspiration will be excluded.

Randomization will be performed using computer-generated random numbers, with group and number assignment being stored in sealed envelopes. An envelope will be drawn in the presence of other staff immediately before the patient enters the operating room. Patients will be randomly assigned into two groups to receive flexible video endoscope intubation (FEI) or Macintosh laryngoscope intubation (MLI). Patients within each group will also be randomized to receive intubation in the left or right lateral decubitus position. Figure 1 shows the flow of the patients through the study.

**Fig. 1 Fig1:**
[figure not shown]
Flow chart of the present study. ASA, American Society of Anesthesiology; BMI, body mass index

### Protocol

The schedule of enrollment, intervention and assessments is shown in Fig. 2. Patients will have standard heart rate (HR), noninvasive blood pressure, and pulse oximetry monitored in the operating room. Penehyclidine hydrochloride 10–12 μg/kg/body weight (maximum dose 1 mg) will be administered after placement of an intravenous catheter. Subsequently, patients will be positioned in either the right or left lateral decubitus position, determined by the site of the surgical procedure, and the patient’s head will be placed in the sniffing position. A pillow, along with a sheet beneath the underside of the head and neck, will be used to maintain the axial alignment, and both arms will be placed perpendicular to the torso over the armrest to support the weight; this position will be maintained during induction of anesthesia and intubation. Following adequate preoxygenation using 100% oxygen via a face mask for 3 min, anesthesia will be induced via an intravenous injection of 1.5–2.5 mg/kg/body weight of propofol and 2.0–4.0 μg/kg/body weight of fentanyl. Rocuronium (0.6 mg/kg/body weight) will be administered for neuromuscular blockade after confirmation of adequate facemask ventilation. Bag-mask ventilation will be continued for 3 min with 100% oxygen and 2% inspired sevoflurane. Neuromuscular blockade depth will be measured using time of flight (TOF) Watch SX acceleromyography. The patient’s oropharyngeal secretions will be cleared with a suction tube after complete muscle relaxation is confirmed using a nerve stimulator, with a TOF value of 0.

**Fig. 2 Fig2:**
[figure not shown]
Schedule of enrollment, intervention and assessments

Two anesthetists, who are not informed about the use of the Macintosh laryngoscope or the flexible video endoscope until the patient arrives in the operating room, will perform all intubations. These anesthetists have experience of > 4000 intubations using the Macintosh laryngoscopes and > 400 using the flexible video endoscope with the patient in the supine position. However, as they have fewer such experiences with the patient in the lateral position, they will practice tracheal intubation in this position using a mannequin before study initiation. A mannequin attached to a baseboard is placed in the right or left lateral position by holding the baseboard at 90° to the horizontal plane. The anesthetists will practice until the trachea of this mannequin could be successfully intubated with a Macintosh laryngoscope and a flexible video endoscope in both lateral positions within 60 s.

In the MLI group, an experienced anesthetist will stand at the head of the operating table to perform laryngoscopy using the Macintosh blade in the standard fashion. External laryngeal manipulation and adjustment of the position of the patient’s head and neck will be performed by other medical personnel as necessary. In the FEI group, a bite block will be positioned between the upper and lower incisors. An experienced anesthetist will stand in front of the patient’s head to perform intubation using a flexible video endoscope (Mindhao Medical Technology Co. Ltd., Zhuhai, China) following standard procedures, with manipulation of the mandibular angle by other medical personnel. Head and neck positions will be adjusted as required.

An assistant will measure the time to intubation, which is defined as the time taken from insertion of the Macintosh blade or flexible video endoscope between the teeth until successful intubation is confirmed by detecting end-tidal carbon dioxide [8]. To maximize patient safety, only one intubation attempt will be performed in the lateral position. If the attempt takes longer than 60 s or the tracheal tube is inserted into the esophagus, it will be deemed a failure, which will be recorded as 61 s [2, 8–10]. Upon failure of the initial endotracheal intubation, facemask ventilation will be performed for 3 min, and anesthesia will be maintained using sevoflurane 2% in oxygen.

All cases of failure of the first intubation in both groups will be followed by the combined use of the Macintosh laryngoscope and flexible video endoscope during the second attempt. An assistant will perform laryngoscopy using a Macintosh blade in the standard fashion and will hold the position to expose the epiglottis regardless of whether the glottis is exposed. Meanwhile, another operator will insert a flexible video endoscope into the mouth and intubate the trachea following standard procedures. If the attempt takes longer than 60 s or the tracheal tube is inserted into the esophagus, it will be deemed a failure. In the case of failed intubation during the second attempt, difficult mask ventilation, or occurrence of desaturation, the patient will be immediately returned to the supine position. The schedule of enrollment and assessments is as in the Standard Protocol Items: Recommendations for Interventional Trials (SPIRIT) Figure (Fig. 1 and Additional file 1: SPIRIT checklist).

### Study outcomes

The primary outcome is the intubation success rate. Secondary outcomes include the intubation time, the anesthesiologist’s evaluation of the ease of the technique (using a visual analog scale (VAS) 0–10 [11]), and perioperative side effects and complications. Frequency of esophageal intubation, lip or dental injury, sore throat, and hoarseness will be recorded by a non-blinded observer. Intubation time will be measured using a stopwatch, and each failed intubation attempt will be recorded as 61 s. Secondary outcomes also include the intubation success rate of the combined use of the Macintosh laryngoscope and flexible video endoscope during the second attempt. The patients will be followed up for 24 h after surgery. 

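### Complication rates are not tied to an intubation attempt, although every first-attempt failure is then exposed to both devices, about five times as often in the Macintosh group at the planning rates

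*Protocol article*

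**What the plan says.** All references are to the protocol article.

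- **Objective (end of Background).** The first aim is to "compare the effects of intubation with a Macintosh laryngoscope to the effects of intubation with a flexible video endoscope" in the lateral position.
- **Groups (Methods).** "Patients will be randomly assigned into two groups to receive flexible video endoscope intubation (FEI) or Macintosh laryngoscope intubation (MLI"). Apart from the left or right position within each group, no other comparison groups are defined.
- **Second attempt (Methods, Protocol).** "All cases of failure of the first intubation in both groups will be followed by the combined use of the Macintosh laryngoscope" and the endoscope together. If that attempt fails, or if mask ventilation is difficult or desaturation occurs, "the patient will be immediately returned to the supine position".
- **Complications (Study outcomes).** "Frequency of esophageal intubation, lip or dental injury, sore throat, and hoarseness will be recorded by a non-blinded observer". Also: "The patients will be followed up for 24 h after surgery".
- **Analysis (Statistical analysis).** "Comparison of various rates will be performed using the chi square" test with Yates correction, or Fisher's exact test.
- **Rule for success (Discussion, limitations).** The success rate refers to the first attempt alone. Success of the combined second attempt is a separate secondary outcome (Study outcomes).

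No equivalent rule is given for complications.

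**The concern.** A comparison of what each device does to the airway needs events that arose while that device alone was in use. Here, patients whose first attempt fails have a Macintosh blade and an endoscope in the mouth together before most complications are assessed. Who goes on to that exposure depends on the randomised device, and the trial expects the two devices to fail at different rates. The extra exposure therefore does not cancel between the groups. It is most unequal when the trial's own hypothesis is true.

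Two things are at stake:

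- A difference in sore throat, hoarseness or injury could be read as a property of the first device when part of it comes from the second attempt.
- Whether an injury was noted at the first or second attempt is known only at the bedside. If it is not written down then, no later analysis can recover it.

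**Working it through.** The plan gives no expected complication rate, so it has no figure of its own to reproduce on this point. The inputs below are taken as stated; how 87 per group was derived does not matter here.

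**Inputs (Statistical analysis)**

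- Patients per group: 87.
- Planning success rate, Macintosh: 85.3%, so first-attempt failure is 1 − 0.853 = 0.147.
- Planning success rate, endoscope: 97%, so first-attempt failure is 1 − 0.97 = 0.03.
- Added complication risk from the combined attempt, *e*: **not in the document**. It is assumed, and taken as equal in both groups.

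**Step 1. Expected number with the combined attempt** = n × failure rate

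- Macintosh: 87 × 0.147 = 12.8
- Endoscope: 87 × 0.03 = 2.6
- Ratio: 0.147 / 0.03 = 4.9

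With 78 evaluable per group (87 less 10% dropout) the counts are 11.5 and 2.3, and the ratio is unchanged.

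**Step 2. Difference that the second attempt alone would create.** Suppose the devices carry the same risk *b* at the first attempt. The group rates are then *b* + 0.147*e* (Macintosh) and *b* + 0.03*e* (endoscope). The difference is (0.147 − 0.03) × *e* = 0.117 × *e*.

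| Assumed *e* | Macintosh minus endoscope |
|---|---|
| 10 points | 1.2 points |
| 20 points | 2.3 points |
| 40 points | 4.7 points |
| 100 points (ceiling) | 11.7 points |

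**Step 3. Could this alone give a significant result?** With 87 per group, *b* between 10% and 30% and *e* between 10 and 50 points (both assumed), the chance of P < 0.05 in the direction of Macintosh being worse is about 4% to 19%. This uses a two-sided 5% test and the normal approximation without continuity correction. With no difference at all, the nominal chance in that direction would be 2.5%. The 19% needs *b* = 10% and *e* = 50 points, giving rates of 17.4% and 11.5%.

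**Step 4. Rare injuries.** If the combined attempt added a 10-point risk of lip or dental injury (assumed), the expected extra events would be 12.8 × 0.10 = 1.3 and 2.6 × 0.10 = 0.3, a gap of about one event. That is small in absolute terms, but it could be much of the observed contrast if such injuries are rare.

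**Step 5. Which outcomes can be separated.**

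- *Esophageal intubation* is a failure criterion at the first attempt and again at the second (Methods, Protocol). It must already be identified at each attempt to classify success.
- *Lip or dental injury* can largely be assigned to the attempt at which it is noted.
- *Sore throat and hoarseness* are reported after all attempts and cannot be split.

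**The case against.** The strongest defence is that comparing all randomised patients is valid as it stands. Both groups follow the same rescue rule, and needing rescue is a consequence of the assigned device. The comparison therefore answers a sensible question: what happens to patients when one starts with one device or the other. On this view the second-attempt exposure is a downstream effect of the device and not a bias. **This stands** for sore throat and hoarseness, where the main analysis should not change. What remains is that the article frames the objective as device against device and never says that its complication comparison includes the rescue.

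A second defence is that recording by attempt is detail for the case report form or the full protocol, and a condensed article may omit it. **This stands in part.** However, the article does fix attempt rules for first-attempt success, for second-attempt success and for the time recorded after a failure, and leaves only complications without one.

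A reader might also infer three stronger things that the text does not support:

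- *That each complication is counted once per patient, pooled over attempts.* The article speaks only of frequency and is silent on this.
- *That an esophageal placement at the combined attempt is charged to the first device.* No such rule is stated, and the event is already identified separately at each attempt.
- *That a further intubation follows the return to supine and adds to the exposure.* Only the return to supine is stated.

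**Conclusion.** The point holds as a modest, inexpensive improvement to secondary outcomes. The article does not tie complications to an attempt, and at its own planning rates the combined attempt would reach about 12.8 of 87 Macintosh and 2.6 of 87 endoscope patients. Second-attempt events would then add 0.117 × *e* to the difference between groups, or 2.3 to 4.7 points if *e* is 20 to 40 points. That range rests on an assumed *e*, on an equal added risk in both groups, and on the planning success rates holding in the trial.

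It would go too far to conclude that the safety comparison is invalid or cannot inform the device question. At the planning rates, 85.3% and 97% of patients are intubated at the first attempt with the assigned device alone. A blade injury from the combined attempt being counted against the endoscope could arise in only about 2.6 expected patients. The primary outcome is not affected.

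**What to change.** 1. **Record by attempt.** Note esophageal intubation and lip or dental injury against the attempt at which they are noted. No new examination is needed.
2. **Compare on the first attempt.** For these two outcomes, compare the devices on first-attempt events with all randomised patients in the denominator. Report second-attempt events with the combined-technique outcome.
3. **Label the throat outcomes.** Keep the comparison of sore throat and hoarseness in all randomised patients. State that it compares first device plus common rescue, and report beside it the number rescued in each group. Do not exclude rescued patients, since that would break the randomised comparison.

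Suggested text:

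> *Esophageal intubation and lip or dental injury will be recorded by attempt. The groups will be compared on first-attempt events in all randomised patients; second-attempt events will be reported with the combined technique. Sore throat and hoarseness will be compared in all randomised patients as outcomes of the first device plus common rescue, with the number rescued in each group.*

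**Cost.** One more field on the form and a short analysis paragraph, with no change to sample size or treatment. Recruitment is under way (Trial status), so the field will be incomplete for patients already treated, and the number affected should be reported. Some lip or dental injuries will not be assignable to an attempt with certainty and should be shown as such.

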The structure and mode of operation of the Macintosh laryngoscope and the flexible video endoscope are different; therefore, the use of the flexible video endoscope for tracheal intubation with the patient in the lateral position may result in greater success compared with that using a Macintosh laryngoscope. For patients in whom tracheal intubation is difficult in the lateral position, laryngoscopes can be used to increase the space of the pharynx and expose the epiglottis, and subsequently, tracheal intubation can be performed more easily using the flexible video endoscope because of its flexibility of operation.

In conclusion, in this clinical trial, we aim to evaluate the efficacy of intubation using a Macintosh laryngoscope and a flexible video endoscope with the patient in the lateral position and investigate the feasibility of using both devices in combination, when endotracheal intubation in the lateral position has failed with one device. The results of the trial will improve the success rate of tracheal intubation in the lateral position.

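### Sore throat and hoarseness are assigned to a non-blinded observer although masked recording is feasible, so these two secondary device comparisons are open to avoidable ascertainment bias

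*Protocol article*

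**What the plan says.** The protocol article's Abstract (Methods) lists among the secondary outcomes "perioperative side effects and complications, such as frequency of esophageal intubation, lip or dental injury, sore throat, and hoarseness". The Study outcomes section fixes who records them: the list ends "sore throat, and hoarseness will be recorded by a non-blinded observer". The same section adds "The patients will be followed up for 24 h after surgery", without saying who makes the contact or how.

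The Statistical analysis section plans a test between groups: "Comparison of various rates will be performed using the chi square", Yates-corrected, and Fisher's exact test is named as the alternative, at the 5% level.

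Three further statements bear on whether masking is possible:

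- Protocol section: "anesthesia will be induced via an intravenous injection of 1.5–2.5 mg/kg/body weight of propofol". This comes before either device is inserted.
- Methods: "An envelope will be drawn in the presence of other staff immediately before the patient enters the operating room".
- Protocol section, describing the operators: "who are not informed about the use of the Macintosh laryngoscope or the flexible video endoscope until the patient arrives in the operating room". This delays the operators' knowledge of the device. It does not mask the assessment of outcomes.

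**The concern.** One sentence gives the same recording rule to two kinds of outcome. Esophageal intubation and lip or dental injury are noted around intubation by people who can see the device, so masking is not realistic. Sore throat is a symptom that only an awake patient can report, and hoarseness is judged after the tube is out. Both fall in the follow-up period, away from the device, where the obstacle to masking no longer applies.

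An observer who knows the device may prompt for mild symptoms, or count borderline ones, differently in the two groups. A difference in recorded frequency could then reflect the recording and not the device, and a significance test cannot separate the two. The article gives no reason for unmasked recording of these symptoms, and the limitations in its Discussion do not mention it.

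What is at stake is the interpretation of two secondary harm comparisons. The primary outcome, intubation time, esophageal intubation and lip or dental injury are not part of this point.

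**Working it through.** **Step 1: the text.** The plan states no figure for this point, so the first check is to set its statements side by side.

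| Question | Sore throat, hoarseness | Esophageal intubation, lip or dental injury |
|---|---|---|
| When noted | After surgery, within 24 h | Around intubation |
| Patient sees device in use | No, already anaesthetised | No, already anaesthetised |
| Recorder must see device | No | In practice yes |
| Rule in plan | Non-blinded observer | Non-blinded observer |
| Tested between groups | Yes | Yes |

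The rule is avoidable only in the first column. It is stated outright, so it is not a detail left to a fuller document.

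**Step 2: an illustration of size.** The documents give no symptom rates and no measure of recording error. Everything below is assumed except the 87 per group and the Yates-corrected test at 5%, which come from the Statistical analysis section.

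Let the true rate be p in both groups, and let unmasked recording separate the observed rates by g, so that they become p + g/2 and p − g/2. With n = 87 per group, let X and Y be independent binomial counts with these rates. The false-positive rate is the sum of P(X = x)·P(Y = y) over all tables (x, y) whose Yates-corrected chi-square exceeds 3.84.

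| True rate p | Gap g | Observed rates | False-positive rate |
|---|---|---|---|
| 30% | 0 | 30% vs 30% | 3.3% |
| 30% | 5 points | 32.5% vs 27.5% | 8.1% |
| 30% | 10 points | 35% vs 25% | 24.5% |
| 30% | 15 points | 37.5% vs 22.5% | 51.6% |
| 20% | 10 points | 25% vs 15% | 30.9% |
| 40% | 10 points | 45% vs 35% | 22.9% |

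The figure with no gap is below 5% because the Yates correction is conservative.

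**Step 3: under-recording only.** Suppose the observer adds no false cases but records 90% of true cases in one group and 70% in the other. At p = 30% the observed rates are 0.90 × 30% = 27% and 0.70 × 30% = 21%, a 6-point gap. By the same enumeration, the false-positive rate is about 8% at p = 20%, 11% at p = 30% and 16% at p = 40%.

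**Step 4: fewer patients analysed.** The 87 per group allows for 10% dropout. With 0.90 × 87 ≈ 78 per group and p = 30%, the 5-point and 10-point figures fall to about 7% and 22%. The pattern does not change.

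**The case against.** The strongest case on the other side has five parts.

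- **Limited reach.** These are two items in a list of secondary side effects. The primary outcome is decided by a 60 s limit, tube placement and end-tidal carbon dioxide. The plan discloses the unmasked recording and nowhere claims masking. All of this stands, and it limits the weight of the point.
- **The size is assumed.** The recording gaps are put in by hand. With under-recording only, 90% recorded in one group and p = 30%, a 10-point gap means 27% against 17% observed, so only 17/30 ≈ 57% of cases recorded in the other group. That is strong bias. This stands: the larger figures are illustrations, not estimates.
- **No stated motive.** A reader might infer that the team expects fewer throat symptoms with the endoscope, since the Discussion says its use "may result in greater success compared with that using a Macintosh laryngoscope". That sentence concerns intubation success. The hypothesis in the Background is non-directional, and no passage predicts throat symptoms for either device. No direction of bias can be read from the documents.
- **Patient masking is not stated.** The envelope is drawn while the patient is still awake, and the article never says whether patients learn the device. This stands. Masking has to be arranged as well as assumed possible.
- **The recording may already rest on self-report.** The patient may simply be answering the observer, and the form of the follow-up contact is not described. That is possible, but an observer who knows the device still decides how to ask and what to record.

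None of these removes the central fact that the plan prescribes unmasked recording of two subjective outcomes where masking is feasible.

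**Conclusion.** The point holds in a limited form: the comparisons of sore throat and hoarseness are open to ascertainment bias that could largely be avoided at low cost. The conclusion rests on the recording rule as written, on induction preceding device insertion, and on both symptoms arising after surgery.

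A reader might go further and infer that these results will be biased, or biased towards the endoscope. The documents do not support that, because they give no symptom rate, no recording error and no expectation about throat symptoms. The false-positive rates of 3%, 8% and 24% at gaps of 0, 5 and 10 points show only how sensitive the planned test would be if recording differed between groups. The change is worth making, but it does not bear on the validity of the main result.

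**What to change.** Split the sentence in Study outcomes.

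- Keep the non-blinded observer for esophageal intubation and lip or dental injury.
- Record sore throat and hoarseness by patient self-report to a question with fixed wording, within the 24 h follow-up, on a form that does not show allocation.
- State that patients are not told the device, and carry out the envelope draw so that it does not reveal the device to them.
- If staff must ask the question, use existing ward or recovery staff who were not present at intubation.

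The cost is a protocol wording change and a short form. No additional assessor is needed, although the article does not describe the follow-up contact, so the sponsor should confirm that the form fits into it.

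The downside is that the Trial status section says recruitment is under way, so the change mixes two ways of recording. The article does not say how many patients are already enrolled. Show these two outcomes separately for patients before and after the change, and state the unmasked recording as a limitation for the earlier patients.
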